## Sham-controlled Post Standing group III (normal standing posture with natural chest breath adjustment)

Sham-controlled *Post Standing* group III training has the same requirements as sham-*Post Standing* group II training, except for breathing adjustment training, which will use natural chest breathing and then only regulating breathing to make it slow, fine, and continuous.

### Training quality monitoring and duration

The 14-week training program will include both centralized and supervised training. Centralized training will last two weeks, with five 30-min sessions per week. Participants in the different groups will learn the key adjustments known as “regulating body, breath, and mind” and all ancillary practices until they master them under the guidance of coaches. After centralized training, participants will practice supervised training for the remaining 12 weeks, with five 30-min sessions per week. Coaches will supervise training to ensure correct practice. Participants will be required to complete a training self-evaluation log, which will include assessing the difficulty of training; the level of relaxation or tension or pain and fatigue in different parts of the body; perspiration levels; saliva secretion; body warmth sensation; breath control state; meditative state of mind; and any abnormal physical and mental reactions during and after training.

Feasibility will be assessed based on the number and content of training self-evaluation log entries per day. Compliance and attendance will also be monitored using training sign-in sheets to assess attendance rates. To eliminate bias from excessive physical activity (PA), all participants in both groups will be asked to record their PA (type and intensity of activities, duration of sedentary time, and sleeping hours) in diaries during the training period.

### Participant recruitment and enrolment

Participants will be recruited using various methods including online social media platforms, schoolyard advertisements, recruitment posters, health education lectures, and school radio announcements. Additionally, leaflets and brochures will be distributed, providing a brief introduction to the trial and the researchers’ contact information. During the screening phase, interested college students will contact the research assistants by telephone or email. Two trained and accredited investigators will repeatedly assess their sleep quality using two assessment scales (PSQI and ISI) and then determine eligibility for participation. Research assistants will provide written information about the study and explain the objectives, specific procedures, potential adverse effects, and expected benefits to potential participants. They will also enquire about their interest in joining the study. If the applicant meets the study criteria, they will be required to sign a written informed consent form prior to enrolment. Additionally, participants will be informed that they can withdraw from the study at any time during the trial period. Each participant will receive a logbook to monitor their involvement and training practices, and they will be asked to report any adverse events (AEs).

### Blinding method

In this trial, the coaches delivering the training will not be involved in the outcome assessments but they cannot be blinded to group allocation. However, to blind the recruited participants, sham-controlled *Post Standing* groups will be established, with participants unaware of the features of Qigong exercises and basic mind–body standards and practices of TCPS. Prior to group allocation, all training coaches will discuss with each participant that all forms of training may benefit them. Four blinding codes, "A," "B," "C," or "D," will be used to blind the data collectors, outcome assessors, and statistician, who will not be involved in group allocation and training implementation.

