### Eligibility criteria

This study aims to recruit full-time college students aged 18 to 26 with normal hearing and right-handedness who meet the Diagnostic and Statistical Manual of Mental Disorders, Fifth Edition (DSM-V) criteria for insomnia disorder. They must have sleep difficulties at least three times per week for a minimum of three months, with impaired daytime functioning and a PSQI score above 5 and an ISI score above 7. Participants must be willing to participate, understand study requirements, and provide informed consent in accordance with the Declaration of Helsinki. The inclusion and exclusion criteria are shown in Table 2.

**Table 2 Tab2:** Inclusion and exclusion criteria

Inclusion criteria	Exclusion criteria
**Eligible participants who meet the following criteria will be included: Participants matching any of the following criteria will be excluded:**	
• Full-time college students, aged between 18 and 26 years • Right-handed, either sex • Normal or corrected to normal hearing	• Engaging in long-term regular practice (regular practice defined as a frequency of at least three times a week and at least 30 min per session) of *Post Standing* or other traditional Chinese mind–body exercises, or any kind of physical activity and muscle strength training at least six months prior to study enrollment
• Fulfilling the diagnostic criteria for insomnia disorder (including difficulty in initiating sleep, maintaining sleep, or early morning awakening with inability to return to sleep, complaints of impaired daytime functioning and sleep difficulty occurring at least three times per week for a minimum of 3 months) according to the DSM-V	• Being in a member of martial arts, dance, aerobics, sanda, taekwondo, and other similar clubs or associations
• PSQI score > 5 and ISI score > 7 • Willing to participate in the study and understand and provide signed informed consent forms according to the Declaration of Helsinki	• Presence of secondary insomnia caused by smoking addiction, drug or alcoholic abuse or dependence, stress disorder, personality disorder, psychoactive substances and non-addictive substances, neurological or psychiatric disorders or other underlying diseases or symptoms such as cervical spondylosis, fever, cough, and pain symptoms

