• Able to understand the study process, complete weekly sessions/modules of the intervention program on a regular basis, cooperate with the scale assessments and measurement of EEG, plantar pressure and biomechanical balance, and physical function	• Presence of another sleep–wake disorder (e.g., narcolepsy, restless leg syndrome, a breathing-related sleep disorder, a circadian sleep–wake rhythm disorder, a parasomnia) • Irregular learning and living schedules over the prior four weeks such as staying up late or internet addiction • Have a history of chronic headache and migraine, primary and secondary brain injury, head trauma, and familial psychosis • Taking any medication or healthcare products or receiving other sleep-related non-pharmacotherapy to improve sleep quality at least two weeks prior to study entry • Suffering from malignant tumors or other serious consumptive diseases, autoimmune diseases, infectious diseases, neurological or psychiatric disorders, serious organic disease, or other chronic physical diseases including cardiovascular disease, pulmonary, renal, hepatic or gastrointestinal disease, or hematopoietic system diseases, musculoskeletal system diseases, or other contraindications to exercise • Pregnant, breastfeeding, or planning to conceive within the study period
	• Implantation of active metal or pacemaker or defibrillator in the body that affects measurement and assessment • Skin integrity at the electrode placement site is impaired or allergic to electrode gel or adhesive • Unable to perform breath training due to the onset of acute respiratory disease or other reasons • Participated in any other academic studies or clinical trials in the past 8 weeks or participating in any other academic studies or clinical trials during the study period • Any other circumstances that the investigators believe may make the participant unable to complete, comply with, or unsuitable for this study

*Abbreviations: DSM-V* Diagnostic and Statistical Manual of Mental Disorders, Fifth Edition, *PSQI* Pittsburgh Sleep Quality Index, *ISI* Insomnia Severity Index, *EEG* electroencephalogram

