## Discussion

This protocol describes the first double-blind parallel RCT aiming to evaluate the efficacy, safety, and feasibility of using TCPS for sleep quality improvement in college students with insomnia. Compared with the diverse Qigong modalities used to treat insomnia in the literature, using TCPS to treat insomnia in college students has the following advantages. First, TCPS is a static form of Qigong that requires minimal space and can be practiced by college students in places like dormitories or outdoors. It can also be easily incorporated into the study day, such as during the commute or study breaks, thereby encouraging its practical application. Second, TCPS is easy to learn and has a low risk of injury, contingent upon adherence to the correct taught posture and respiratory principles. This makes it optimal for independent and persistent practice by college students. Third, within the university milieu, insomnia tends to emerge as a consequence of the psychophysiological consequences of academic obligations and sociocultural interactions. Our previous research has shown that TCPS has therapeutic effects on anxiety symptoms in the college population through regulation of respiratory function, correction of body balance, and augmentation of autonomic nervous system function [20–22]. Thus, TCPS has distinct advantages in ameliorating sleep disturbances amongst this specific demographic by bolstering both physical resilience and psychological welfare.

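### Participant blinding presumes students do not know TCPS, but the eligibility criteria screen for the amount of regular practice, not for previous instruction

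*Protocol article*

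**What the plan says.** The Introduction places aim 1 in a sham-controlled, double-blind setting. The Blinding method section says that coaches cannot be blinded. Participants are blinded through three sham Post Standing groups, "with participants unaware of the features of Qigong exercises and basic mind–body standards and practices of TCPS". Before allocation, "all training coaches will discuss with each participant that all forms of training may benefit them". Data collectors, outcome assessors and the statistician see only the codes A to D.

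No inclusion criterion asks that a student be new to Qigong or TCPS. The relevant exclusions in Table 2 (Eligibility criteria) are:

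- long-term regular practice of Post Standing, of other traditional Chinese mind–body exercise, or of physical activity generally, with "regular practice defined as a frequency of at least three times a week and at least 30 min per session"; the sentence ends "any kind of physical activity and muscle strength training at least six months prior to study enrollment";
- membership of martial arts, dance and similar clubs;
- "Participated in any other academic studies or clinical trials in the past 8 weeks", or concurrent participation in another study;
- a general clause for anyone the investigators consider unsuitable.

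The primary outcomes are PSQI and EEG (Study setting and procedure). PSQI, ISI and SF-36 are questionnaires that the participant answers (Outcome assessment; Follow-up period).

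**The concern.** The blind depends on what participants know, while the exclusion criterion measures how much they have trained. The two differ. Someone who has been taught TCPS can recognise it whether or not they ever practised three times a week.

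This matters because the participant supplies the PSQI score. A student who recognises the authentic form, or who recognises that normal standing or chest breathing is not it, may rate sleep with that in mind. Randomisation balances the number of such students across arms in expectation, but not their reaction to the arm they receive, which arises after allocation. The A-to-D coding does not reach a score that the participant provides.

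The Introduction makes earlier exposure plausible: it describes TCPS as a well-regarded, often practised form and Post Standing as basic to many Qigong exercises.

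**Working it through.** The plan gives no figure on this point, so the check sets the criteria against the blinding premise and asks which students with earlier knowledge of TCPS each criterion removes.

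1. **Regular-practice exclusion.** It requires at least three sessions a week and at least 30 minutes per session. The six-month wording is ambiguous: it may be a minimum duration or a look-back window.
   - Post Standing twice a week, for any length of time: 2 < 3 sessions, so not excluded on either reading.
   - A short TCPS course below the weekly frequency or session length, then stopped: not excluded on either reading.
   - Three times a week for three months: excluded or not, depending on the reading. The point does not rely on this case.
2. **Club exclusion.** It removes a student taught TCPS only if they also belong to a listed or similar club.
3. **Other-study exclusion.** It removes anyone in another study within the past 8 weeks. A person taught Post Standing in a study that ended earlier is not caught here, and is caught under item 1 only if that practice met the threshold and the six-month term.
4. **Investigator discretion.** It permits exclusion of a TCPS-trained student but does not require it.
5. **Baseline data.** General demographic characteristics include physical activity habits and club membership. These are recorded, and neither is a question about TCPS instruction.

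Taken together, at least two plain profiles (practice twice a week; a short course below threshold) pass every mandatory criterion while failing the condition stated in the Blinding method section.

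**Which knowledge separates the arms.** All four arms are taught body, breath and mind adjustment, so general familiarity with Qigong does not tell a participant which arm they are in. Knowledge of TCPS itself can: its posture distinguishes TCPS and sham group I from sham groups II and III, and its abdominal breathing distinguishes TCPS and sham group II from sham groups I and III. This is why the gap concerns Post Standing and TCPS instruction in particular.

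**Size.** As a simple approximation, the expectation bias in a TCPS-versus-sham contrast on PSQI is the proportion of participants who recognise their form multiplied by the average shift in their score difference that recognition causes. The document gives neither term. A further effect can run the other way: a previously taught student in a sham arm may practise the authentic form, which would pull the contrast towards zero. Neither the size nor the net direction can therefore be calculated.

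**The case against.** The strongest reply is that the blind does not rest on naivety alone. The comparators are three standing-and-breathing programmes. Sham group I shares the TCPS posture and mind adjustment, and sham group II shares its breathing, so partial knowledge would not cleanly separate the arms. The coaches' talk is aimed directly at expectation. The club and discretionary exclusions would remove some experienced students, and EEG, the other primary outcome, is not self-rated. All of this stands and limits the concern. It does not close the gap, because none of these measures obliges the trial to turn away a student who has been taught TCPS.

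Four stronger readings are tempting and are not supported:

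- A reader might infer that the double-blind comparison has failed. The text shows only that one of its conditions is assumed rather than ensured.
- The Discussion says "Our previous research has shown that TCPS has therapeutic effects on anxiety symptoms in the college population", and a reader might infer that former participants will enter this trial. The article states no campus, date or overlap. The 8-week bar leaves this possible, and no more.
- Research assistants will "explain the objectives, specific procedures, potential adverse effects, and expected benefits to potential participants", and a reader might infer that consent itself unblinds. This is ordinary consent content. The article does not say that TCPS is named as the active form or that any arm is called sham, and the participant-facing wording is not shown.
- A reader might attach a number, for example 10–30% recognising their form and a shift of 1–2 points, giving 0.10 × 1 = 0.1 to 0.30 × 2 = 0.6 PSQI points. Every input there is an assumption, so the result says nothing about this trial.

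**Conclusion.** The point holds in a limited form. The protocol article blinds participants on the premise that they do not know TCPS, and its eligibility criteria do not secure that premise. Students taught Post Standing or TCPS below the practice threshold are eligible, whichever way the six-month term is read. This leaves PSQI, ISI and SF-36 open to expectation bias of unknown size and uncertain net direction. EEG is not self-rated and so is not open to this route.

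The conclusion assumes that some eligible students have had such instruction and that some of them would recognise their form. The document makes the first plausible but quantifies neither. The change is worth making because it closes a mismatch between two stated rules at little cost. The finding does not show that the blind is broken.

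**What to change.** In Table 2, take Post Standing out of the frequency-based criterion. Exclude any previous instruction in or practice of Post Standing, Zhan Zhuang or TCPS, including participation at any time in an earlier Post Standing or TCPS study. Keep the frequency threshold for other exercise.

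Optionally, add one question at weeks 8 and 14 asking which form participants believe they are practising, so that the double-blind claim can be checked against data.

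The cost is an amendment to one exclusion criterion, a slightly smaller recruitment pool and, if adopted, one extra questionnaire item at two visits.

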### Trial design

This will be a prospective, double-blinded, randomized controlled trial with a parallel four-arm design. Participants will be randomized to either TCPS or one of three sham-controlled *Post Standing* exercises. Participants and data collection/analysis personnel will be blinded to the intervention allocation.

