## Intervention training methods

### Standardized TCPS group (TCPS posture with abdominal breath adjustment)

Standardized TCPS group training will consist of three elements: body, breath, and mind adjustments. As seen in the standardized *TCPS* shown in Fig. 2, body adjustment consists of ball encircling training, which requires holding the arms as if embracing a tree, with the palms facing inward about two feet from the chest. The participants look forward or slightly downward and chooses a high, medium, or low stance, depending on individual fitness. The feet are planted firmly on the ground as if standing on a well stone; deep rooted and unshakable. Breath adjustment starts with a normal natural breath and gradually transitions to abdominal breathing and reverse abdominal breathing, with a slower respiratory rhythm and rate and increased volume and depth as the posture gradually lowers. Mind adjustment requires concentrating on the three circular configurations with a relaxed demeanor.

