## Sham-controlled Post Standing group I (TCPS posture with natural chest breath adjustment)

Sham-controlled *Post Standing* group I also consists of three elements: body, breath, and mind adjustment, where the body and mind adjustment training are the same as the standardized TCPS exercise. However, breath adjustment requires mainly using natural chest breathing and then only regulating breathing to make it slow, fine, and continuous.

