#### Synchronous detection procedure

Different groups of participants will be required to follow the pre-recorded guided voice instructions to practice body, breath, and mind adjustments in sequence. It should be noted that all participants at baseline will simply imitate the training practice under the pre-recorded guided voice instructions. Synchronous detection, including plantar pressure and biomechanical balance, physical function, and neurophysiological assessments, will be performed during the three-minute resting and relaxed standing state before the training practice state with self-active adjustment, the five-minute standing practice state with self-active adjustment, and the three-minute resting and relaxed standing state after the standing practice state with self-active adjustment. The stability of the instrument during the synchronous detection procedure will also be recorded.

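### The arm codes cannot blind the staff who run the week 8 and week 14 laboratory recordings, because participants perform their assigned posture during them

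*Protocol article*

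**What the plan says.** The Trial design section of the protocol article makes the claim in general terms: "Participants and data collection/analysis personnel will be blinded to the intervention allocation". The Blinding method section names the roles and the device. Codes A to D "will be used to blind the data collectors, outcome assessors, and statistician", and these people take no part in allocation or training. The same section accepts that coaches cannot be blinded and keeps them apart from measurement: "the coaches delivering the training will not be involved in the outcome assessments". It describes no other masking device and no other separation of roles.

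The section Synchronous detection procedure sets out the laboratory session: "Different groups of participants will be required to follow the pre-recorded guided voice instructions to practice body, breath, and mind adjustments in sequence". The recording is defined as "Synchronous detection, including plantar pressure and biomechanical balance, physical function, and neurophysiological assessments", taken over three minutes of resting standing, then "the five-minute standing practice state with self-active adjustment", then three more minutes of resting standing. Table 1 places these assessments at baseline, week 8 and week 14. The section Study setting and procedure names EEG as a primary outcome alongside PSQI.

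**The concern.** A letter code hides allocation only from someone who cannot tell the arms apart in another way. Here the arms are defined by how a person stands and breathes, and the session records them while they do so. Staff who know the arm can, without intending it, vary how they instruct or encourage a participant, when they repeat a recording, or how they handle a poor signal. EEG is a primary outcome, so readers who take the double-blind label at face value would credit it, and the plantar and physiological measures, with a protection that these sessions lack.

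**Working it through.** No arithmetic decides this point, and the plan gives no figure to reproduce. The check sets the blinding statement against the measurement procedure.

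1. **When allocation could be revealed.** The section Randomization and allocation concealment puts randomization after the baseline assessment, so baseline recordings have no allocation to reveal. That leaves two laboratory visits, weeks 8 and 14. Weeks 18 and 22 have no laboratory recording in Table 1.

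2. **What is visible.** The TCPS group is described as "holding the arms as if embracing a tree, with the palms facing inward about two feet from the chest". For sham I, "the body and mind adjustment training are the same as the standardized TCPS exercise". Sham II and sham III stand naturally with the arms hanging at the sides. Posture therefore splits the arms into {TCPS, sham I} and {sham II, sham III}. Sight of the posture alone does not separate the two arms within a pair.

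3. **What separates the arms within a pair.** TCPS and sham II use abdominal breathing; sham I and sham III use natural chest breathing. The section on plantar pressure and physical function lists chest and abdominal amplitudes and movements among the recorded signals. Anyone watching or reading that signal can probably tell the two arms apart.

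| Posture | Abdominal breathing | Chest breathing |
|---|---|---|
| Three-circle | TCPS | Sham I |
| Normal standing | Sham II | Sham III |

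4. **How much of the session is exposed.** The recording lasts 3 + 5 + 3 = 11 minutes, of which 5 are practice. Seeing the practice state is enough to inform the operator, whichever part of the recording is later analysed.

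5. **What happens to the code.** Four codes for four arms means, on the natural reading, one letter per arm. With 100 participants allocated 1:1:1:1, each letter covers 100 / 4 = 25 people. Linking a letter to a posture narrows it to one pair of arms. Linking it to posture and breathing together can identify the arm for all 25.

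6. **Which outcomes are touched.** The outcomes from this session are EEG, plantar pressure and balance, respiratory function, HRV, blood pressure and oxygen saturation. PSQI, ISI and SF-36 are self-reported questionnaires. They fall in the same study weeks, but the article does not say that they are completed in the same session or with the same staff.

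**The case against.** **The signals come from instruments, and processing can be done blind.** The Neurophysiological assessment section describes software preprocessing and power-spectrum analysis, which can be run from coded files by people who never attend a session. A condensed article may leave the split between operator and processor to the full protocol. This stands as far as it goes: offline EEG processors and the statistician can remain masked, and instrument recording limits bias. It does not rescue the claim for data collectors, whom the article expressly says are blinded.

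**The exposure is inferred.** The article does not say in so many words that operators watch the participant, that the voice instructions differ by arm, or that staff can hear them. That is correct, and the point does not rely on the instructions being heard. It relies on the ordinary expectation that someone running a standing EEG and pressure-plate recording can see the person being recorded. No screening is described.

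**Stronger readings.** A reader might infer that the laboratory outcomes as a whole are unblinded, that all four arms are identified on sight, or that the sleep outcomes are compromised because the same staff collect them. The documents support none of these. Later roles can stay masked, sight gives two pairs only, and the questionnaires are self-reported with no stated shared session. Nor does the article describe manual artefact rejection, so operator judgement in EEG handling is a possibility to close off and not a documented fault.

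**Recording during practice is part of the mechanistic aim.** The Discussion wants brain activity while participants engage in TCPS. This is accepted, and nothing here asks for the practice recording to be dropped.

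**Conclusion.** The stated blinding does not hold for the staff who run the synchronous recording at weeks 8 and 14. The letter codes are weakened for anyone who can link a letter to a posture and a breathing pattern. This bears on the EEG primary outcome and on the plantar, respiratory, HRV, blood pressure and oxygen saturation outcomes. PSQI, ISI and SF-36 are at most indirectly affected.

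The exposure covers both post-randomization laboratory visits for every participant attending them. The resulting bias cannot be sized from the document. The conclusion rests on two assumptions: that session operators can see the participant, and that each letter belongs to one arm. It should be corrected, because the claim is explicit and the remedy is cheap, but it does not invalidate the design.

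**What to change.** - State that laboratory session operators are not blinded. Limit the claim to participants, offline EEG processors and the statistician.
- Label recordings with random participant IDs that carry no arm letter.
- Have EEG preprocessing and artefact handling done from those files, under criteria fixed in advance, by existing personnel who do not attend the sessions.
- Have PSQI, ISI and SF-36 self-completed before the recording session.
- Keep the statistician on coded arm labels, as now.
- Acknowledge that plantar and respiratory files from the practice state may themselves reveal the arm, so removing the letter does not fully mask them.

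The cost is revised wording, a set visit order, a small re-coding step, and written EEG criteria. The downside is a narrower blinding claim. The choice of EEG segment for the between-arm comparison is a separate question and need not change for this reason.
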